## Abstract

Multiple factors make adherence to antiretroviral therapy (ART) a complex process. This study aims to describe the barriers and facilitators to adherence for patients receiving first-line and second-line ART, identify different adherence strategies utilized and make recommendations for an improved adherence strategy. This mixed method parallel convergent study will be conducted in seven high volume public health facilities in Gauteng and one in Limpopo province in South Africa. The study consists of four phases; a retrospective secondary data analysis of a large cohort of patients on ART (using TIER.Net, an ART patient and data management system for recording and monitoring patients on ART and tuberculosis (TB)) from seven Johannesburg inner-city public health facilities (Gauteng province); a secondary data analysis of the Intensified Treatment Monitoring Accumulation (ITREMA) trial (a randomized control trial which ran from June 2015 to January 2019) conducted at the Ndlovu Medical Center (Limpopo province); in-depth interviews with people living with Human Immunodeficiency Virus (PLHIV) who are taking ART (in both urban and rural settings); and a systematic review of the impact of treatment adherence interventions for chronic conditions in sub-Saharan Africa. Data will be collected on demographics, socio-economic status, treatment support, retention in care status, disclosure, stigma, clinical markers (CD4 count and viral load (VL)), self-reported adherence information, intrapersonal, and interpersonal factors, community networks, and policy level factors. The systematic review will follow the Preferred Reporting Items for Systematic Reviews and Meta-Analysis (PRISMA) reporting and Population, Interventions, Comparisons and Outcomes (PICO) criteria. Analyses will involve tests of association (Chi-square and t-test), thematic analysis (deductive and inductive approaches) and network meta-analysis. Using an integrated multilevel socio-ecological framework this study will describe the factors associated with adherence for PLHIV who are taking first-line or second-line ART. Implementing evidence-based adherence approaches, when taken up, will improve patient’s overall health outcomes. Our study results will provide guidance regarding context-specific intervention strategies to improve ART adherence.

## Introduction

Inconsistent adherence to treatment is a contributing factor to poor health outcomes of people affected by numerous health conditions, including HIV, tuberculosis, diabetes mellitus (DM) and hypertension [1–3]. The World Health Organization (WHO) defines adherence as the degree to which a patient is able to follow a treatment schedule and take medication at recommended times [4–6]. In the context of HIV, lapses in adherence to medication can lead to the development of viral rebound, which can result in immunosuppression and viral resistance [4,7–9].

WHO recommends the use of the HIV drug dolutegravir (DTG) as the preferred first-line and second-line ART treatment regimens for all populations due to its formidable resistance barrier and improved tolerability [10–12]. Despite the advantages of this first-line regimen, in South Africa between 20%-30% of patients with HIV experience clinical, immunological or virological failure from first-line ART due to lapses in adherence [13–15]. This is a concern because of the clinical and cost implications attached to treatment failure [16,17].

Adherence to ART is a complex process that is affected by multiple factors, and numerous studies have attempted to establish what the barriers and facilitators of ART adherence are [18–20]. Individual-level factors such as age, sex, ethnicity, HIV status disclosure and forgetfulness, have been reported as important in predicting ART adherence [21]. However, using individual-level factors one is only able to report a limited proportion of the variability in non-adherence [22]. Good interpersonal relationships between patients and care givers or treatment supporters including healthcare providers, an intimate partner, family members, and friends have been reported as predictors for good adherence [22,23]. In contrast to intrapersonal and interpersonal factors, the community level factors such as poverty, HIV related stigma and discrimination against patients on ART introduce barriers to ART adherence [24]. Additional to community level factors, awareness of healthcare policy level factors like HIV treatment guidelines, policies, and best practices are imperative in ensuring good adherence and maintenance of the continuum of care [25].

### Conceptual framework

Various studies have demonstrated that there are many factors that play an important role in maintaining adherence behaviour [26–29]. These factors have been explored using several models, including: 1) Anderson’s Health Care Utilisation model [30], which is a framework that considers predisposing factors (individual’ own personality and behaviour), enabling factors (patient and health provider relationship, community education) and need factors (patient’s beliefs, alternative medicine treatment options, community support); 2) the Dahlgren-Whitehead ’rainbow model’ [31], a model that builds the relationship between the individual, the environment they live in and health; 3) Information-Motivation-Behavioural skills model (IMB model) [32–34], a model that views adherence behaviour as a function of the interrelations between adherence-related information, motivation, and behavioural skills; 4) the socio-ecological conceptual framework [35,36], which takes into consideration the individual, and their connections to other people, and how they adapt their behaviour to the social environment. This model suggests that an individual’s behaviour is cohesive in a dynamic network of intrapersonal, interpersonal characteristics, community features and existing health policies [35,36].

Our study will adapt the socio-ecological conceptual framework to investigate multilevel and interactive factors such as individual/intrapersonal, interpersonal, community, and health policy level factors that affect adherence to ART (Fig 1). It will explore the different aspects of these factors that act either as barriers or facilitators of adherence to ART.

**Fig 1 pone.0261107.g001:**
[figure not shown]
An adapted socio-ecological framework. An adapted socio-ecological framework that depicts the layers of individual, relationship, community, and healthcare policy level factors which influence the processes of treatment adherence and retention in care [36].

#### Intrapersonal level factors

The intrapersonal level of the socio-ecological conceptual framework comprises individual knowledge, attitudes, beliefs, perceptions, and skills that influence behaviour [35]. It further includes age, sex, income, mental health, education, substance use, spirituality, comorbidities and past experiences [36].

#### Interpersonal level factors

Here the participant’s social network or relationships with other people including family, friends, peers, intimate partner and health care providers [35] are included. This level also highlights trust and communication as factors that builds a relationship between patients and care givers or treatment supporters [25].

#### Community level factors

The components of the community-level factors that may influence patient’s adherence to ART incorporate cultural views and social norms towards ART access, HIV related stigma, poverty, and available support services within the community [36].

#### Policy level factors

The public policy level is shaped by local, and government laws regarding access and adherence to ART. The socio-ecological conceptual framework reports on awareness of macro level factors which includes health policies, HIV treatment guidelines and best practices, [22,36].

### Research gap

Although ample literature on adherence to ART has been available for a while, there remains a dearth of studies relating to the multi-level factors associated with adherence to treatment and processes shaping adherence behaviour, particularly in South Africa. This lends to the lack of understanding of the interplay between the various factors involved at different levels of the treatment taking behaviour of the ART patient.

In South Africa specifically, there is lack of reported knowledge about the effectiveness and impact of strategies currently employed to promote adherence in people living with HIV (PLHIV) who are taking ART (particularly young patients, males, and those experiencing severe treatment related side effects) [37,38]. Unfortunately, there are no quantitative studies of combination ART in South Africa (and even sub-Saharan Africa more generally) that have used a social-ecological perspective or approach. This is despite the understanding that patients on ART require comprehensive adherence strategies and strict viral load monitoring [39,40].

Until 2017, there were minimal related treatment adherence strategies (routine blood monitoring, targeted adherence counselling, and adherence clubs [41–43]) employed by the South African government [41]. However, effectiveness of these interventions have not been widely reported on. Additionally, the patients’ perspectives seem to be given little consideration in the adherence intervention development and implementation. It is therefore important to assess effectiveness of existing strategies from the perspectives of PLHIV taking ART in order to recommend and develop relevant and acceptable strategies to patients [44,45]. This is evidenced in a study conducted in Malawi which highlighted how critical it is for health programmers to prioritize adherence view points from patients as part of strengthening the clinical monitoring strategy used [46].

### Rationale for the study

Consistent high levels of adherence to HIV medication are important for viral suppression, consequently preventing resistance to ART and progression of the illness [47]. According to the socio-ecological framework, numerous levels of factors affects patients’ adherence to treatment [25]. Therefore, a multilevel socio-ecological framework will provide information about the influence of particular risk factors relative to others, or if combined effects of risk factors are additive or related. The socio-ecological framework will serve as the conceptual framework in our study in order to understand factors affecting treatment adherence at different levels and also guide strategies to improve ART adherence.

#### Aim

To describe the barriers and facilitators to adherence for patients receiving first-line and second-line ART and different adherence strategies utilised.

#### Overarching hypothesis

A socio-ecological framework combined with multi-model data collection will identify the barriers and facilitators to ART adherence and retention in care for PLHIV needed to strengthen adherence interventions.

### Research questions and hypotheses

What are the demographic characteristics and clinical indicators associated with virological failure and being lost to follow-up (LTFU) in PLHIV taking first-line and second-line ART in urban communities?Hypothesis: Demographic and clinical characteristics are associated with virological failure and being LTFU in patients on ART from complex, and highly mobile urban communities.What are the intra-and inter-personal factors (demographic, socio-economic characteristics), social and community level factors (poverty, social norms, HIV related stigma, culture), structural factors (health systems, support services) and clinical indicators associated with self reported adherence, pill count and virological failure to first-line and second-line ART in rural communities?Hypothesis: Individual and community level factors are associated with self-reported non-adherence, suboptimal pill count, and virological failure in patients on ART in the rural setting.What are the perspectives of virally suppressed and unsuppressed first-line and second-line ART patients about treatment adherence in selected urban and rural communities?
Are there any differences between people receiving first-line and second-line ART?Are there any differences in treatment taking behaviours between virally suppressed and unsuppressed ART patients?What do virally suppressed and unsuppressed ART patients recommend as adherence strategies?Hypothesis: In South African communities, treatment taking behaviour, perceptions of adherence, and recommendations for adherence interventions differ between PLHIV who are virally unsuppressed and those who are virally suppressed.What treatment adherence strategies and interventions have been implemented and evaluated in sub-Saharan Africa for HIV, hypertension, and DM?Hypothesis: There are no differences in the effectiveness of adherence interventions implemented in sub-Saharan Africa for HIV, hypertension, and DM.

## Materials and methods

### Study design

The study will employ a mixed method parallel convergent approach conducted in four phases (I-IV). Due to the different approaches for each study objective, we present the study methods based on each objective. While the studies will employ their own separate methods, all the results will be converged/collated into a single discussion to provide recommendations for adherence strategies that can be rolled out in South Africa.

### Materials and methods: Phase I

Objective 1: Assess demographic characteristics and clinical indicators associated with virological failure and LTFU in first-line and second-line patients in an urban community.

#### Study design

The study will employ a quantitative retrospective cohort study using secondary data analysis of data on people with HIV taking ART (18 years and older) recorded in the TIER.Net database.

TIER.Net is the monitoring and evaluation system used by the South African Department of Health for ART patient and data management. It comprises limited demographic information and all treatment and laboratory information from the time of commencement on HIV treatment. This is elaborated on in the data collection section.

The South African Department of Health started providing ART in the public health setting on 01 April 2004. From TIER.Net, we will extract a list of all patients who were initiated on ART from 01 April 2004 to 29 February 2020 in the urban setting (city of Johannesburg region F). The cut-off period of 29 February 2020 was chosen to give ART cohorts a minimum of a 12-month follow-up during which a full clinical assessment could be completed as per guidelines.

#### Study setting

This study will be conducted in seven health facilities in the city of Johannesburg region F.

This includes all levels of care

**Primary Health Care**: Jeppe Clinic, Malvern Clinic, Rosettenville Clinic, Yeoville Clinic**Community Health Centre**: Hillbrow Community Health Center (HCHC)**Hospitals**: Charlotte Maxeke Johannesburg Academic Hospital (CMJAH) and South Rand Hospital (SRH)

#### Sampling/Sample size

For this study, all records of people with HIV who were ever initiated on ART between 01 April 2004 (the inception of the South African national HIV treatment programme in the public health setting) and 29 February 2020 from the seven public health facilities will be included. Based on the TIER.Net database, about 130 000 adult patients were initiated on first-line and second-line ART in the seven facilities selected in the city of Johannesburg region F.

#### Data collection

Data will be extracted from the TIER.Net database (as an MS Excel export file). TIER.Net captures demographic information such as patient age, sex, facility name and contact details and also HIV specific information such as HIV diagnosis date, ART start date, regimen at baseline, ART visit dates, CD4 count, viral load done and viral load suppression The system also records all treatment related information, including ART switch. All these variables will be extracted (see S1 Appendix study codebook). The data will be exported to STATA 15.1 for data cleaning and analysis. Records with missing data will be excluded in the final analysis. This will be after conducting all necessary data quality checks, verifications, and triangulations with other data sources.

*Outcome*. VL count is categorized into suppressed (<1000 copies/ml) or unsuppressed (**≥**1000 copies/ml) [48,49]. The status on retention in care for patients will be categorized into active in care, LTFU, transferred out, or recorded dead. For this study, LTFU is defined as having missed a scheduled medical appointment by 90 days or more, as defined by the South African Department of Health [50].

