#### Data analysis

Data will be coded and analysed using STATA version 15.1. Tests of association (Chi-square and t-test) between outcome variables and selected demographics characteristics and clinic indicators will be conducted. Outcome variables will include viral load detectability and retention outcomes (active in care, transferred-out, lost to follow-up and dead),. Regression analysis, univariate and multivariate analyses between variables will be built for outcome variables to identify independent predictors. Variables such as age, sex, health facility, baseline regimen, ART start date, baseline CD4 count, most recent CD4 count, ART visit dates, and months on ART will be considered as predictor variables or independent variables. Analysis will include survival analysis which will consider different entry time points into the ART program. Subsequently, patients will not be grouped all together but will be followed up in a 12-month interval when measuring the outcomes (virological failure and lost to follow up).

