#### Strengths and limitations

To our knowledge this will be the first study using a social-ecological perspective and a convergent parallel mixed method design to report on combination ART in South Africa. Combining quantitative and qualitative data from public health settings, a controlled environment, the patient perspective and evidence from the region will enable us to make recommendations for a comprehensive, acceptable, and appropriate adherence strategy for the country.

The study presents a fewlimitations. The study will be conducted in a total of eight health facilities (seven of over 120 health facilities in one South African metropolitan municipality (urban setting) and one facility in a rural setting). Therefore, findings may not be generalizable to other municipalities and districts in South Africa, or to other country settings. Furthermore, although there are efforts to ensure good quality of data by the South African Department of Health, supporting partners and research staff, secondary data are subject to quality issues, due to data inconsistencies and missing data. Other potential predictors of adherence, such as disclosure, stigma, and self-reported adherence, will be assessed through a standard questionnaire. This may lead to reporting bias (memory and social desirability biases). Policy-level factors might not probe for relevant factors due to how this study is designed (with it focus on the individual’s awareness of health policies and guidelines which is insufficient to fully assess policy-level factors).

In conclusion, our study will demonstrate how an existing socio-ecological conceptual framework can be used as a tool to provide guidance regarding facilitators and barriers to ART adherence. By populating this framework through secondary data analysis, participant interviews of PLHIV who are taking ART and a systematic review comparing adherence intervention strategies for the chronic conditions, this mixed method study will provide evidence on factors affecting treatment adherence at different socio-ecological levels and guide context-specific intervention strategies to improve ART adherence. We believe that the use of our study results to strengthen adherence intervention will subsequently improve health outcomes and decrease the number of patients switching to complex treatment such as second-line and third-line regimens.

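### Phase I's unrestricted exclusion of records with missing data can select on loss to follow-up, and it conflicts with the plan to include everyone who started ART

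*Protocol article*

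**What the plan says.** All references are to the protocol article, Materials and methods: Phase I, unless stated otherwise.

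- **Sampling/Sample size** takes in every person recorded as starting ART at the seven facilities between April 2004 and February 2020, about 130 000 adults.
- **Data collection** lists the extracted fields, among them "ART visit dates, CD4 count, viral load done and viral load suppression", and then gives the missing-data rule: "Records with missing data will be excluded in the final analysis". One qualifier follows: "This will be after conducting all necessary data quality checks, verifications, and triangulations with other data sources".
- The same section defines the retention outcome: "LTFU is defined as having missed a scheduled medical appointment by 90 days or more".
- **Data analysis** treats viral load and retention status as outcomes, measured over 12-month intervals. Among the candidate predictors, "baseline CD4 count, most recent CD4 count, ART visit dates, and months on ART will be considered as predictor variables".
- **Strengths and limitations** concedes that "secondary data are subject to quality issues, due to data inconsistencies and missing data", but attaches no remedy and no sensitivity analysis.

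**The concern.** The unit that is dropped is the record, and nothing confines the rule to the variables a given model uses. Some extracted items depend on staying in care. A patient who leaves before the first follow-up test has no follow-up viral load and may have no CD4 beyond baseline. Checking and triangulation can recover a result that was never captured, but not a test that was never done.

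For such patients the missing value is a consequence of leaving care, which is itself an outcome of the analysis. Excluding them tilts the LTFU analysis towards people who stayed long enough to be tested. Because outcomes are measured in 12-month intervals, the effect would be greatest in the first interval. Factors that act on early disengagement could be weakened or lost, and the size of the cohort would give a biased figure a narrow interval.

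There is also a plain conflict of text: one section includes everyone who started ART, and the next removes any record with missing data.

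**Working it through.** The plan gives no LTFU rate, no missing-data rate and no power calculation, so there is no figure of its own to reproduce. All rates and effect sizes below are assumptions; only the cohort size of about 130 000 comes from the article.

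**1. LTFU proportion.** Let L be true LTFU, mL the probability of an incomplete record in lost patients, and mR that probability in all others (active, transferred, dead).

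Observed LTFU = L(1−mL) / [L(1−mL) + (1−L)(1−mR)]

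Lost share of dropped records = L·mL / [L·mL + (1−L)·mR]

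With L = 30%:

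| mL / mR | Calculation | Observed LTFU | Lost share of dropped records |
|---|---|---|---|
| 60% / 10% | 0.12 / (0.12 + 0.63) | 16.0% | 72% |
| 50% / 20% | 0.15 / (0.15 + 0.56) | 21.1% | 52% |
| 40% / 10% | 0.18 / (0.18 + 0.63) | 22.2% | 63% |
| 40% / 30% | 0.18 / (0.18 + 0.49) | 26.9% | 36% |
| 20% / 20% | 0.24 / (0.24 + 0.56) | 30.0% | 30% |

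Over the four unequal pairs, a true 20% becomes 10.0–17.6% and a true 40% becomes 22.9–36.4%. The bias is downward whenever mL exceeds mR, and zero when they are equal.

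**2. Apparent precision.** In the 60%/10% case, 130 000 × 0.75 = 97 500 records remain. The 95% half-width is 1.96 × √(0.16 × 0.84 / 97 500) = 0.0023, or 0.23 percentage points, around an estimate that is 14 points too low.

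**3. Odds and risk ratios.** Assume an LTFU risk of 25% in unexposed and 40% in exposed patients: OR 2.00, RR 1.60. Keep mR at 10% in both groups.

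- mL 50% in both groups: odds are 0.125/0.675 and 0.20/0.54, so the OR is 0.370/0.185 = 2.00, unchanged. The RR moves to 0.270/0.156 = 1.73.
- mL 40% unexposed, 60% exposed: OR = (0.16/0.54)/(0.15/0.675) = 1.33.
- mL 30% unexposed, 60% exposed: OR = (0.16/0.54)/(0.175/0.675) = 1.14.
- mL 60% unexposed, 40% exposed: OR = (0.24/0.54)/(0.10/0.675) = 3.00.

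Selection on the outcome alone leaves the OR intact. Missingness that depends jointly on outcome and predictor can move it either way.

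**4. Hazard ratios.** One simulation per row: 30 000 patients, 40% exposed, 12 months of follow-up, baseline monthly hazard 0.05 for six months and 0.012 afterwards, first viral load assumed at six months.

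| Early HR / late HR | LTFU: all → all early losses dropped | HR: all → all early losses dropped | HR: 60% of early losses dropped |
|---|---|---|---|
| 1.5 / 1.5 | 35.6% → 8.1% | 1.50 → 1.48 | 1.56 |
| 2.0 / 1.0 | 38.4% → 7.0% | 1.75 → 0.91 | 1.70 |
| 2.0 / 1.5 | 39.1% → 8.0% | 1.92 → 1.50 | 1.98 |

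With all early losses dropped, the model sees only the late effect, so the 0.91 is a random draw around the built-in 1.0. The HR is distorted when early and late effects differ and early losses are removed completely. Under partial removal it changes little, although LTFU still falls to 21–24%.

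**The case against.** The strongest reply is that the rule may be meant model by model: a record is dropped only where a variable in that model is missing. Viral load is an outcome in Phase I and is not listed as a predictor of LTFU. Whether a viral load was done is extracted separately from its result, so an untested patient could be coded as not done. The most recent CD4 can be the baseline value. The Sampling section points the same way. This reading is possible, but the sentence does not say it, and a model that requires most recent CD4 could still select on staying in care.

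Second, Objective 1 concerns factors associated with LTFU and virological failure, and the clearest bias is in the LTFU proportion. That is fair. The effect on associations is conditional, as the working shows.

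Third, a reader might infer that the rule removes mainly patients lost early. The article does not support that. It gives no missingness by retention status, and lost patients are 72% of dropped records in one scenario but 36% in another. Missing baseline fields would also cause exclusion. Early deaths and transfers would too, and because they count among the patients who are not lost, they narrow the gap between mL and mR. The supportable word is disproportionately.

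Finally, the planned checks and clean-up with facility staff, and the stated limitation, do reduce or disclose recording gaps. They do not help with tests never performed. Imputation detail may properly sit in an analysis plan that is not shown, but the exclusion rule itself is stated here and is the point at issue.

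**Conclusion.** The point stands in this form. As written, the rule covers the whole record, can select on LTFU, and contradicts the inclusion of everyone who started ART. The LTFU proportion is biased downward whenever incompleteness is more common in lost patients, which is likely where leaving care prevents testing. A true 30% would appear as about 16–27% under the assumed rates; the actual size cannot be computed from the article.

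A reader might go further and infer that the predictor estimates are necessarily biased. That does not follow. An OR is unaffected by selection on outcome alone, and an HR that is constant over time is nearly preserved. Bias arises when early and late effects differ or when missingness depends jointly on LTFU and the predictor. Either is possible here, and the plan offers no means of detecting it.

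**What to change.** Replace the exclusion sentence in Phase I Data collection with the following, and reconcile it with Sampling/Sample size:

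1. Every patient who started ART stays in the LTFU and retention analysis, without any requirement for a follow-up viral load or most recent CD4.
2. Completeness is required only for the variables each model needs.
3. Missing baseline covariates, such as baseline CD4, are handled by multiple imputation, with complete-case analysis as a sensitivity analysis. The exact specification can be left to the analysts.
4. Viral load is analysed among those tested, and the untested share is reported by retention status. Weighting for being tested is an option.

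The cost is revised wording and modest extra programming on data already held; no new data are needed.

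### Phase I virological failure is analysed only among patients with a viral load in the interval, because records without one are excluded; associations are biased if testing depends on both the predictor and failure

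*Protocol article*

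**What the plan says.** The Phase I objective names two outcomes: "Assess demographic characteristics and clinical indicators associated with virological failure and LTFU in first-line and second-line patients in an urban community".

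The outcome paragraph under Phase I, Data collection, gives the virological variable two levels: "VL count is categorized into suppressed (<1000 copies/ml) or unsuppressed", the second level being 1000 copies/ml or more. Leaving care is held in another variable: "The status on retention in care for patients will be categorized into active in care, LTFU, transferred out, or recorded dead". Loss is defined by appointments: "LTFU is defined as having missed a scheduled medical appointment by 90 days or more". The same section gives the only rule for absent values: "Records with missing data will be excluded in the final analysis". This follows data quality checks and triangulation with other sources.

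Phase I, Data analysis, lists the outcomes side by side: "Outcome variables will include viral load detectability and retention outcomes (active in care, transferred-out, lost to follow-up and dead". It adds: "Analysis will include survival analysis which will consider different entry time points into the ART program". It then says that patients "will be followed up in a 12-month interval when measuring the outcomes (virological failure and lost to follow up".

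The article does not say how loss, death, transfer or an untested interval enters the failure analysis. It also gives no separate definition of virological failure for Phase I, so the 1000 copies/ml cut-off is the only one available.

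**The concern.** A two-level viral load variable needs a viral load. In any 12-month interval, four kinds of patient may lack one: those lost, those transferred out, those who died before a test, and those in care but untested. The missing-record rule removes them from the binary failure analysis.

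Removal would do little harm if it were unrelated to failure. The article's own reasoning suggests that it is related. Its Introduction attributes treatment failure to lapses in adherence, and loss means an appointment missed by at least 90 days. The first hypothesis expects demographic and clinical characteristics to be associated with both virological failure and loss. A characteristic that drives patients out of care could then look unrelated to virological failure, because the patients through whom it acts have been dropped. Phase I feeds the adherence recommendations, and about 130 000 records would put narrow confidence intervals around a biased estimate.

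**Working it through.** The article gives no rate of loss, death or missing viral load and no effect size for Phase I, so there is no figure of its own to reproduce. Every rate below is an assumption, apart from the cohort size.

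**1. Who is left out.** Let m be the share with no viral load in the interval. If m is 5% to 30%, then 0.05 × 130 000 = 6 500 to 0.30 × 130 000 = 39 000 patients have no virological score.

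**2. Bounds on the proportion failing.** With f the failure proportion among tested patients, failure in all patients lies between f(1 − m) and f(1 − m) + m. For f = 20%:
- m = 5%: 19.0% to 24.0%
- m = 20%: 0.20 × 0.80 = 16.0% to 16.0% + 20.0% = 36.0%
- m = 30%: 14.0% to 44.0%

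**3. A null result among tested patients.** Take two equal-sized groups, each with 12% unsuppressed among tested patients, so the tested-only risk ratio is 1.00. Let L be the share lost, all before a viral load, and q the share of lost patients who are unsuppressed. Everyone not lost is taken as tested. The risk over all patients is L × q + (1 − L) × 0.12.

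| Lost, A vs B | q | Risk A | Risk B | Ratio B/A | Mean of A and B |
|---|---|---|---|---|---|
| 10% vs 20% | 50% | 0.050 + 0.108 = 0.158 | 0.100 + 0.096 = 0.196 | 1.24 | 17.7% |
| 10% vs 20% | 100% | 0.100 + 0.108 = 0.208 | 0.200 + 0.096 = 0.296 | 1.42 | 25.2% |
| 20% vs 40% | 50% | 0.100 + 0.096 = 0.196 | 0.200 + 0.072 = 0.272 | 1.39 | 23.4% |
| 20% vs 40% | 100% | 0.200 + 0.096 = 0.296 | 0.400 + 0.072 = 0.472 | 1.59 | 38.4% |

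**4. A true effect, and when the bias disappears.** Let true failure be p = 30% in one group and 20% in the other: odds ratio (0.30/0.70)/(0.20/0.80) = 1.71, risk ratio 1.50. Let a share l be unmeasured, with failing patients k times as likely to be unmeasured as others. Non-failing patients are then unmeasured with probability u = l/(pk + 1 − p), and failure among tested patients is p(1 − ku)/(1 − l). For p = 0.30, l = 0.30 and k = 2: u = 0.30/1.30 = 0.231 and failure among tested is 0.30 × 0.538/0.70 = 0.231. The composite column counts every unmeasured patient as a failure.

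| Unmeasured | k | Tested-only OR (true 1.71) | Tested-only RR (true 1.50) | Composite RR |
|---|---|---|---|---|
| 15% vs 15% | 1 | 1.71 | 1.50 | 1.27 |
| 15% vs 15% | 2 | 1.74 | 1.54 | 1.27 |
| 15% vs 15% | 3 | 1.79 | 1.59 | 1.28 |
| 30% vs 15% | 1 | 1.71 | 1.50 | 1.59 |
| 30% vs 15% | 2 | 1.40 | 1.31 | 1.54 |
| 30% vs 15% | 3 | 1.21 | 1.17 | 1.51 |
| 30% vs 5% | 1 | 1.71 | 1.50 | 2.12 |
| 30% vs 5% | 2 | 1.25 | 1.20 | 1.98 |
| 30% vs 5% | 3 | 1.00 | 1.00 | 1.89 |

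With equal loss, or with loss unrelated to failure (k = 1), the tested-only association is unbiased or nearly so. When loss differs between groups and is linked to failure, it moves towards the null here, completely so in the last row. The composite is not the truth either: it is too low with equal loss and too high at 30% vs 5%. In these nine settings the true risk ratio lies between the two estimates or equals the tested-only one. That supports showing both, but it is not a general bound.

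**The case against.** The strongest objection is the planned survival analysis. In a time-to-event model, a patient who leaves before a viral load can contribute follow-up until censoring or a competing event, so it is not established that such patients vanish from every failure analysis. That stands as a limit on the claim. It does not remove the problem: the article describes the survival analysis only in terms of entry times and gives no rule for censoring or competing events. Plain censoring at loss would still assume that loss is unrelated to failure.

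A second objection is that an article leaves such details to the full protocol, and that the codebook in the S1 appendix is not shown. That would answer a complaint about silence. Here the exclusion of records with missing data is stated, without any limit to covariates.

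A reader might infer that failure is scored only in patients retained in care. The text does not support this. A patient tested and then lost or dead in the same interval is scored, and a patient in care but untested is not. The selection is on testing. The illustration in step 3 assumes no lost patient was tested first, so it is at the unfavourable end on that point.

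A third objection concerns the remedy. The hypothesis describes the urban population as highly mobile, so some patients counted as lost may be on treatment elsewhere without a recorded transfer. Counting them all as failures can overstate failure, and it blurs two outcomes that the objective names separately. This stands, and it is why the composite belongs in a sensitivity analysis.

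The article's limitations mention missing data in general, but not that the failure result depends on who was tested.

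**Conclusion.** The point holds in a limited form. As written, the binary Phase I failure analysis is conditional on having a viral load in the interval, and the missing-record rule makes this a stated choice. Associations are biased only where testing depends on both the predictor and failure; the study's own hypothesis and its account of failure make that plausible but do not prove it.

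The size is unknown. Under the assumptions of step 3, a tested-only risk ratio of 1.00 corresponds to 1.24–1.42 with 10% vs 20% lost and to 1.39–1.59 with 20% vs 40% lost. The overall proportion unsuppressed rises from 12% to about 18–25% and 23–38% respectively. With equal loss of 15%, a true odds ratio of 1.71 is estimated at 1.71–1.79, which is close to unbiased. The documents do not support saying that Phase I will certainly miss or reverse a predictor. They do support saying that, as described, it could not show whether it had.

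**What to change.** 1. State that the missing-record exclusion does not apply to a viral load that is absent because of loss or death.
2. Label the planned binary analysis 'among patients with a viral load in the interval'.
3. Add a sensitivity analysis for all patients at risk at the start of each 12-month interval, with the outcome 'in care with viral load <1000' versus 'viral load ≥1000, LTFU or dead'. Censor recorded transfers, show patients in care but untested as a separate row, and use the same baseline predictors.
4. State the censoring and competing-event rules for the survival analysis of virological failure.
5. Report the tested-only and composite results side by side and read them as a range.

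The cost is some wording, one more outcome definition, one model and one table. Retention status, visit dates and viral load are already available from the extraction. The downside is that the composite mixes loss with viraemia and may overstate failure among mobile patients treated elsewhere without a recorded transfer, so it should not replace the tested-only result.
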